### Aims and Hypotheses

The goal of this study is to develop an improved SCI PrU risk model to better predict level of risk, guide preventive practices, and ultimately maximize the patient’s clinical outcomes. The resultant risk model, tailored to veterans with SCI, should promote adoption into clinical practice.

We will test two hypotheses to compare a model based on the commonly used Braden Scale versus (1) a risk model developed using structured data alone and (2) a model using both structured and NLP (ie, semistructured and unstructured) data. A third hypothesis will test the added value of NLP-based data over structured data. The hypotheses are as follows:

1. Hypothesis 1: The risk model using structured data alone will predict the development of PrUs better than the model based on the Braden Scale.

2. Hypothesis 2: The risk model based on combined structured and NLP data will predict the development of PrUs better than the model based on the Braden Scale.

3. Hypothesis 3: The risk model based on combined structured and NLP data will predict the development of PrUs better than the model based on structured data alone.

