### Variables Selection and Definition—Ongoing

The dependent variable for this study will be documentation of the occurrence of a PrU in the EHR within 1 year (ie, 1-year incidence risk of PrU). The definition of the presence of a PrU used for case identification is based on ICD-9-CM codes (707.0-707.9) and the application of the classification algorithm based on text analysis or a combination of these two sources, depending on what is found to be more accurate. The potential independent variables for this study include the risk factors that were identified through a literature review and validated by expert panel discussion. The final list of potential risk factors, with input from the expert panel, will be extracted from multiple tables in the EHR, or from semistructured and unstructured text notes, for use in analysis. Three sets of candidate predictors based on data sources will be generated to develop each risk model: (1) structured data extracted directly from the EHR, (2) Braden scores, and (3) a combination of existing structured data and data extracted from text through the NLP processes.

The investigators conducted a comprehensive literature review generating a list of approximately 50 potential independent variables or risk factors (eg, demographics, diseases status, comorbidities, health behaviors, psychosocial factors, and home care). This list was reviewed by the expert panel for logical consistency, completeness, clinical relevance, and whether they were modifiable or not. The panel identified high-priority risk factors and discussed practical considerations including where the risk factor might be located in the EHR, how reliable these data might be, and alternative ways to document risk factors. Subsequently, persistent moisture on the skin, the type of living situation of the patient, evidence of malnutrition, and documentation that the patient took steps to redistribute their weight during the day were targeted as risk factors available in unstructured data. Structured data contained elements of the Braden Scale, lab values, and other variables (see Table 1). Several coding systems are used to classify structured data variables, including the ICD-9-CM, Logical Identifiers Names and Codes (LOINC), and the Healthcare Common Procedural Coding System (HCPCS). International Classification of Diseases, Tenth Revision, Clinical Modification (ICD-10-CM) codes were not implemented in the VHA until after the end of this study and are not used.

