### Sample and Sampling—Complete

Using VHA data in its Corporate Data Warehouse obtained through its Veterans Affairs Informatics and Computing Infrastructure (VINCI), we identified an inception cohort (N=12,344) of veterans with SCI who received care in the VHA in FY 2009, but had no PrU in the 12 months prior to 2009 based on recorded ICD-9-CM codes. This group was considered free of PrUs for the purpose of the study. All structured hospital discharges (N=4090), outpatient encounters (N=5,202,804), and text data (N=9,888,245) for the cohort for FY 2009-2013 (October 1, 2008-September 30, 2013) were obtained through the VINCI. Veterans from this cohort were classified as having a PrU (ie, PrU+) or not having a PrU (ie, PrU-) during the study period based on both structured and text data. A total of 3860 PrUs were identified based on structured data and 829 based on text data alone, resulting in a total incidence of 4689 (4689/12,344, 37.99%) across the study period.

**Table 1 table1:** Risk factors categorized by structured, semistructured, and unstructured data sources.

Data source	Risk factor	Description or definition
Structured	Age	Age in years
	Gender	Male/female
	Race/ethnicity	Race/ethnicity
	Education level	Highest level of education
	VHA^a^ eligibility	VHA category, service connection
	Body weight	Body mass index, most recent weight, or change in weight
	Patient status	Inpatient/outpatient when pressure ulcer develops
	Pattern of preventive care	Consistency of annual well-patient exam
	Cognitive dysfunction	ICD-9-CM^b^ codes (ie, traumatic brain injury, dementia, and Alzheimer’s disease)
	Comorbidities—psychological	ICD-9-CM codes (ie, depression, anxiety, and posttraumatic stress disorder)
	Comorbidities—physical	ICD-9-CM codes (ie, diabetes mellitus, pulmonary disease, cardiac disease, renal disease, peripheral vascular disease, anemia, deep vein thrombosis, cancer, infection, lower extremity fractures, spasticity, autonomic dysreflexia, hypotension, and heterotopic ossification)
	Laboratory analysis	LOINC^c^ codes for lab values (ie, C-reactive protein, white blood cells, erythrocyte sedimentation rate, renal function, hemoglobin, hematocrit, albumin, and prealbumin)
	Medications	VHA formulary to identify chemotherapeutics, steroids, and benzodiazepines
	Surgery	ICD-9-CM codes of surgical procedures within previous 6 months of pressure ulcer development (administrative data)

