### Data Analysis—Planned

Three separate predictive models of PrU occurrence based on each set of predictors in each hypothesis will be developed using R statistical program version 3.3.2 (The R Foundation). To prepare, the distribution of each continuous predictor will be examined and variable transformation will be carried out as appropriate to approximate normality (eg, log transformation of skewed data). However, to avoid information loss, no continuous variable will be categorized in an initial prognostic model. Using the generalized additive model (GAM) approach, a bivariate logistic regression will be performed to test potential nonlinearity between each continuous candidate predictor and the binary PrU outcome [25]. This will provide further guidance for appropriate transformation needed for the predictor.

The analytic data sample (N=12,344) will be randomly divided into two groups in the ratio of 70% (n=8641) for derivation and 30% (n=3703) for validation. The randomization will be stratified by site, age group, and gender to increase similarity in the distribution of both validation and derivation random samples.

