Data analysis will be focused on testing two hypotheses that compare the ability of the current standard risk assessment measure—Braden Scale—with models based on structure data alone and in combination with data extracted from text. Comparisons will be made between a pair of risk models to test each hypothesis using exactly the same veterans from the validating sample. Our priority will be to develop models with low false positive rate (ie, the rate at which negative instances are incorrectly classified as having PrU). This consideration will guide how any two competing risk models (ie, classifiers) will be compared using the receiver operating characteristic (ROC) curve analysis. The logistic model will output proper probability scores from which a full ROC curve will be generated for each classifier with overlay in one plot. Generally, a higher calculated total area under the curve (AUC) implies a better prognostic performance. However, when comparing two classifiers, it is possible for the classifier with a higher total AUC to show poorer local performance in our priority region. Therefore, we will assess classifier performance in the overall AUC as well as partial AUC (pAUC) in our priority local region of low false positive rate. The classifier that has a higher sensitivity (ie, true positive rate) in the priority region has superior local performance. That is, an appropriate pAUC will also be computed in addition to the standard full AUC.

Both discrimination and calibration will be investigated as validation measures for each prognostic model using the validation sample. The better discriminating models have higher AUC and pAUC values based on their CIs (ie, better able to distinguish between patients with SCI who have and do not have PrU). To assess calibration, the predictions of each model will be compared with the veterans’ actual outcomes in the validation sample by performing the Hosmer-Lemeshow test using the hoslem.test function in the Resource Selection library of R. To ensure that the overall type I error rate of α is maintained, first, we will repeatedly sample from each model and calculate the Hosmer-Lemeshow *P* value 1000 times, and calculate the proportion of *P* values less than .05 (ie, type I error rate should be no greater than 5%).

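### Model discrimination is to be judged from the models' own AUC and pAUC intervals although the models are scored on the same veterans; a paired interval for the difference should be the stated criterion, chiefly for Hypothesis 3

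*Protocol article*

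**What the plan says.** Aims and Hypotheses lists three comparative hypotheses: structured data against Braden, structured plus NLP data against Braden, and, as Hypothesis 3 has it, "The risk model based on combined structured and NLP data will predict the development of PrUs better than the model based on structured data alone".

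Model Development makes the comparison paired: "Comparisons will be made between a pair of risk models to test each hypothesis using exactly the same veterans from the validating sample". Both the full AUC and a partial AUC in a region of low false positive rate are to be assessed, and the low false positive region is described as the priority. The next paragraph, on validation measures, gives the criterion: "The better discriminating models have higher AUC and pAUC values based on their CIs". The article mentions no interval or test for a difference in AUC or pAUC, and no covariance between models. It also does not say how the intervals are to be compared.

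The discussion of hypothesis tests opens with "Data analysis will be focused on testing two hypotheses that compare the ability of the current standard risk assessment measure", which covers only the Braden comparisons. Hypothesis 3 comes under the same procedure because each hypothesis is to be tested by a pair of models.

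**The concern.** Each hypothesis is about a difference between two AUCs estimated on the same people. Such estimates are positively correlated, so the difference is known more precisely than the two separate intervals suggest. If the models are ranked by whether their own intervals overlap, that precision is lost and the real error rate is far below 5%. If the rule means something looser, such as a higher estimate with intervals displayed, it is not a test at any stated level.

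Hypothesis 3 is the most exposed. Its candidate predictors include those of its comparator, so a high correlation and a modest gain are both plausible. A real contribution from the text data could be reported as no difference, and that contribution is a main reason for the study.

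**Working it through.** **Inputs from the article**
- Split: "70% (n=8641) for derivation and 30% (n=3703) for validation". Check: 0.70 × 12,344 = 8640.8 and 0.30 × 12,344 = 3703.2. Both reproduce.
- Events over the study period: 3860 + 829 = 4689, and 4689/12,344 = 37.99%. This reproduces, and gives about 0.3799 × 3703 = 1407 veterans with and 2296 without a PrU in the validation sample.
- The dependent variable is one-year occurrence, but 37.99% covers five fiscal years and no one-year figure is given.
- The article states no expected AUC, AUC difference, between-model correlation or power, so there is no power figure to reproduce.

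**Assumptions**
- AUCs of 0.65 to 0.75; correlation r between the two AUC estimates of 0.5 or 0.8; 95% intervals.
- Event rate of 38%, or 10% as an illustration for one year (370 with, 3333 without). For orientation, a constant yearly risk would give 1 − (1 − 0.3799)^(1/5) = 9.1%.
- The rule is read as non-overlap of separate intervals.

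**Standard error (Hanley-McNeil), AUC 0.70, 1407/2296**
- Q1 = 0.70/1.30 = 0.5385; Q2 = 2 × 0.49/1.70 = 0.5765.
- Variance = [0.21 + 1406 × (0.5385 − 0.49) + 2295 × (0.5765 − 0.49)]/(1407 × 2296) ≈ 0.0000826, so SE ≈ 0.0091. At AUC 0.72, SE ≈ 0.0089. At 10% events the two are 0.0158 and 0.0155.

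**Smallest gap that counts as a difference**
- Non-overlap: 1.96 × (SE1 + SE2).
- Paired: 1.96 × SEdiff, where SEdiff = √(SE1² + SE2² − 2r·SE1·SE2).

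| Events | Non-overlap | Paired, r = 0.5 | Paired, r = 0.8 |
|---|---|---|---|
| 38% | 0.035 | 0.018 | 0.011 |
| 10% | 0.061 | 0.031 | 0.019 |

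With both SEs at 0.0091, the first entry is 3.92 × 0.0091 = 0.036.

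**Power**
- Non-overlap: Φ((d − 1.96(SE1 + SE2))/SEdiff). Paired: Φ(d/SEdiff − 1.96). Here d is the true gap.
- Example, 0.70 against 0.72, 38% events, r = 0.5: SEdiff = 0.0090. Non-overlap Φ((0.020 − 0.0353)/0.0090) = 4.5%; paired Φ(0.020/0.0090 − 1.96) = 60%.

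| Events | AUCs | Non-overlap / paired, r = 0.5 | Non-overlap / paired, r = 0.8 |
|---|---|---|---|
| 38% | 0.70, 0.72 | 4.5% / 60% | 0.4% / 94% |
| 38% | 0.70, 0.73 | 29% / 92% | 19% / >99% |
| 38% | 0.70, 0.75 | 96% / >99% | 99.7% / >99% |
| 38% | 0.65, 0.75 | >99% / >99% | >99% / >99% |
| 10% | 0.70, 0.73 | 2.3% / 49% | 0.1% / 86% |
| 10% | 0.70, 0.75 | 25% / 90% | 14% / >99% |
| 10% | 0.65, 0.75 | 99% / >99% | >99% / >99% |

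With no true difference, the non-overlap rule has a two-sided error rate of about 0.0001 at r = 0.5 (0.0009 at r = 0.3).

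**Check by simulation** (binormal scores, DeLong test, 600 runs): for 0.70 against 0.73 at 38% events and score correlation 0.5, power was 33% under non-overlap and 93% paired. For 0.65 against 0.75 it was 100% both ways.

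Power for the pAUC was not computed, because the article gives no false-positive range.

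**The case against.** The strongest reply is that the article never says non-overlap is the rule. The criterion stands in a paragraph on validation measures for each model, and the preceding paragraph, which governs the hypothesis tests, explicitly sets up paired comparisons. A full analysis plan could name a paired test, and an article may leave the choice of method and the exact pAUC range to it. This stands in part: non-overlap is the natural reading but an inferred one, and every power figure for the current rule depends on it. It does not remove the point, because the article does state a criterion, and that criterion refers to the models' intervals and not to an interval for the difference. The same section goes as far as naming the R function for calibration.

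A reader might infer that most of the power is lost for all three hypotheses. The documents do not support that. At 38% events, gaps of 0.05 or more are detected either way. Hypotheses 1 and 2 compare with a Braden-based model, and the Background reports a ceiling effect, with 91.3% rated high risk, so a large gap there is plausible.

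For Hypothesis 3, only the candidate predictor sets are nested. Automated selection followed by a judgement-based choice may give final models that are not, so a high correlation is plausible but not established.

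Finally, on the non-overlap reading the error is conservative. It can hide a small gain but makes a false claim of superiority less likely, and the AUC estimates themselves are unaffected.

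**Conclusion.** The point holds in limited form. The comparison is paired, but the stated criterion, most naturally read, uses separate intervals and so discards the covariance. On that reading, and with the assumed AUCs and correlations, the gap needed is about two to three times that of a paired interval. The practical loss is for gains of 0.02 to 0.03 at 38% events, which matters chiefly for Hypothesis 3. If one-year events are nearer 10%, it extends to gaps of 0.05, while a gap of 0.10 would still be detected. A general loss of power across Hypotheses 1 to 3 is not shown. This should be fixed before the validation results are seen; it does not invalidate the design.

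**What to change.** Replace the criterion in Model Development with a statement that, for each of Hypotheses 1 to 3, the conclusion rests on:

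- the paired difference in AUC in the validation sample with its 95% CI, by DeLong or by bootstrap of veterans;
- the paired difference in pAUC with a bootstrap 95% CI, over one false-positive-rate range fixed before the ROC curves are seen.

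Intervals for each model can still be reported as description. The pAUC keeps the priority that the plan gives it, and no testing order among the hypotheses is needed for this change. The sentence that introduces the hypothesis tests should name all three hypotheses, so that Hypothesis 3 is plainly covered.

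The cost is a change of wording and a little extra analysis on scores that will exist anyway. No new data are needed, and the article lists the data analysis as still planned.

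### The simulation step said to ensure the Hosmer-Lemeshow type I error rate only measures it, against a flat 5% limit with no allowance for simulation error; 'overall' is left undefined

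*Protocol article*

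**What the plan says.** Data Analysis—Planned sets out three models: "Three separate predictive models of PrU occurrence based on each set of predictors in each hypothesis will be developed". The validation part is "30% (n=3703) for validation". Under Model Development, "Both discrimination and calibration will be investigated as validation measures for each prognostic model using the validation sample", with calibration tested by Hosmer-Lemeshow for each model.

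The error-rate sentence follows: "To ensure that the overall type I error rate of α is maintained, first, we will repeatedly sample from each model". The Hosmer-Lemeshow P value is then to be computed ("value 1000 times, and calculate the proportion of" P values below .05), with the limit given in brackets: "values less than .05 (ie, type I error rate should be no greater than 5" per cent.

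The article does not say whether 'overall' refers to one model's test or to the three together. It gives no tolerance around 5%, and it names no action if the proportion is higher. The next paragraph of the same section adds a calibration plot by tenths of risk, with a smooth curve, a linear fit, and intercept and slope as benchmarks.

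**The concern.** The sentence makes a claim of control, and the step attached to it is a measurement. Simulating outcomes from a model and counting small P values shows how often the test rejects when that model is true. It does not alter the critical value or the P value used on the real 3703 veterans. If the count is too high, the test stays as wrong as before unless something further is done.

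The limit is also set at exactly the nominal value. A simulated proportion scatters around its true value, so a sound test will land above 5% almost as often as below it.

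At stake is how calibration is reported. Hosmer-Lemeshow is the only formal calibration test named, and the models are meant to feed an automated decision support tool, where the predicted probabilities themselves matter. A later statement that the overall type I error rate was held at 5% would not follow from this step.

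**Working it through.** **Inputs from the article.** Three models, each tested on the same validation sample of 3703; 1000 simulated P values per model; cut-off .05; limit 5%. The incidence used for simulation is the study-period figure, "resulting in a total incidence of 4689 (4689/12,344, 37.99%) across the study period". A 10% rate was also tried, because the stated outcome is 1-year risk.

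**Assumptions.** Ten groups for the test (the article gives ten for the plot), chi-square on 10 df for fixed predictions in a separate sample, and perfectly calibrated models. The article does not state the degrees of freedom.

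**1. The plan's own figure.** 5% of 1000 is 50. With the assumptions above and 4000 simulated samples per scenario, each model's rejection rate was 4.4% to 5.5%. The 5% per model is therefore attainable.

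**2. Monte Carlo error of the limit.** For a true size of .05, the standard error of the proportion is √(.05 × .95 / 1000) = 0.0069. The count X is binomial(1000, .05), so P(X > 50) = P(X ≥ 51) = 0.462. The 2.5th and 97.5th percentiles of X are 37 and 64. For other true sizes:

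| True size of the test | P(more than 50 of 1000) |
|---|---|
| 4.0% | 4.9% |
| 4.5% | 19.9% |
| 5.0% | 46.2% |
| 5.5% | 73.0% |
| 6.0% | 89.9% |

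A test of true size 5.5% thus meets the limit in 100 − 73.0 = 27.0% of runs.

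**3. Measuring is not maintaining.** Suppose the reference distribution were chi-square on 8 df while the statistic behaved as chi-square on 10 df. Each test's size would then be P(χ² on 10 df > 95th percentile of χ² on 8 df) = 11.5%. About 115 of 1000 simulated P values would fall below .05, and the check would show this almost surely. The P value reported for the real data would still come from the wrong reference unless a further step replaced it.

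**4. If 'overall' means across the three models.** With each test at exactly .05 and all three models calibrated:

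- independent tests: 1 − 0.95³ = 0.143;
- upper bound: 3 × .05 = 0.15;
- three models scored on the same 3703 veterans, six assumed correlation scenarios: 12.1% to 13.6%.

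The last range depends on assumed relations between the models that the article does not give.

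**5. What the same 1000 datasets can deliver.** Let the Monte Carlo P value be (1 + number of simulated statistics ≥ observed)/1001. It is below .05 only if the numerator is 50 or less. If the model is calibrated, the observed statistic is exchangeable with the 1000 simulated ones, so the size is 50/1001 = 4.995%, whatever the reference distribution.

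**The case against.** **'Overall' may mean the true size of one test.** The procedure described is a standard size check, and the bracketed limit equates the type I error rate with each model's own proportion. This stands. On that reading there is no contradiction, only a misleading word. A reader might infer that the plan promises 5% across models and delivers 13%. The article does not support that as fact, because it never defines 'overall' and any figure near 13% needs an assumed correlation.

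**No decision hangs on the 5%.** The limit is an expectation in brackets with no pass or fail action. This also stands: 46% is the chance of exceeding the stated limit when the size is exactly 5%, not the chance of failing a defined rule. It falls to 4.9% at a true size of 4.0%.

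**The check has some use.** It would reveal gross distortion, as step 3 shows. Agreed, but it cannot separate a sound test from a slightly oversized one.

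**The article is a condensed account, and 'first' implies later steps.** A fuller plan may say what follows. If it already recalibrates the test, the point about maintaining falls away; the flat limit and the ambiguous word remain.

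**Little depends on it.** The hypotheses are compared on AUC and partial AUC, each model's calibration is a separate question, and plots accompany the test. All of this is right, and it limits the weight of the point.

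**Conclusion.** The point holds in a limited form. As described, the simulation step verifies the size of each model's Hosmer-Lemeshow test but cannot ensure it. Its flat limit would be exceeded in 46% of runs by a test of exactly 5% size, a figure that needs only the article's 1000 and 5%. 'Overall' needs a definition: per model, 5% is coherent; across three calibrated models it is not delivered (14.3% under independence, at most 15%, about 12% to 14% under assumed correlations).

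Two stronger conclusions do not follow. The tests of the three hypotheses are not affected. Nor is adjustment across the three calibration tests required, since the article makes no claim about any one of the three failing. This is a small, cheap correction to the formal calibration test.

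**What to change.** 1. For each model, draw the 1000 outcome sets for the validation-sample veterans from that model's predicted probabilities. Compute the Hosmer-Lemeshow statistic each time, and report (1 + number of simulated statistics ≥ observed)/1001 as the P value for the real data.
2. Delete 'overall' and state that the 5% applies per model.
3. If the size check is kept as a diagnostic, flag only proportions above the Monte Carlo limit, that is, more than 64 of 1000.
4. Adjustment across models, for example Holm, is optional.

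**Cost.** A change of wording and a few lines of R, using simulations already planned and no new data. Near .05 the Monte Carlo P value has a standard error of about 0.007 (step 2), so the random seed should be fixed in advance. Holm, if chosen, starts at .05/3 = .0167 and lowers the power to detect miscalibration. For a risk tool that is a real trade-off, only partly offset by the plots.

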**Conclusions:**

To our knowledge, this is the largest cohort employed to identify PrU risk factors in the United States. It also represents the first time natural language processing and statistical text mining will be used to expand the number of variables available for analysis. A major strength of this quantitative study is that all VHA SCI centers were included in the analysis, reducing potential for selection bias and providing increased power for complex statistical analyses. This longitudinal study will eventually result in a risk prediction tool to assess PrU risk that is reliable and valid, and that is sensitive to this vulnerable population.

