A graphical approach will be used to compliment the Hosmer-Lemeshow test since it has been known to be sensitive to sample size. For the graphical method, first, the sample will be divided into 10 risk groups of equal size with each group having similar model predicted probabilities. Next, the observed proportions of PrUs will be plotted against predicted probabilities for these groups with one smooth curve fit (eg, lowess) as well as a linear fit to the data points. We anticipate that the observed and predicted occurrence of PrUs will be similar across the risk groups. A perfect calibration (ie, perfect agreement between the predicted and observed outcomes) will produce a calibration line with an intercept and slope of 0 and 1, respectively [27-29]. The smooth curve will be added to reveal differential calibration among risk deciles, if present.

We expect the validation study to span across different domains (eg, inpatient vs outpatient, site, age group, and gender) as this provided the strongest evidence of generalizability of the prediction rule to new patients [30]. Since stratified randomization ensured a similar case mix within each of our samples—derivation and validation—and both samples were representative of our population of interest, we believe that the results of our validation tests will serve as strong evidence of generalizability.

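### The 70/30 random split stratified by site is internal validation; it does not support the claim of strong evidence of generalizability beyond the same sites and years

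*Protocol article*

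**What the plan says.** The section Sample and Sampling—Complete describes a single source: "we identified an inception cohort (N=12,344) of veterans with SCI who received care in the VHA in FY 2009". The records "for the cohort for FY 2009-2013 (October 1, 2008-September 30, 2013) were obtained through the VINCI".

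Under Data Analysis—Planned, this sample "will be randomly divided into two groups in the ratio of 70% (n=8641) for derivation and 30% (n=3703) for validation". The purpose of the stratification is stated: "The randomization will be stratified by site, age group, and gender to increase similarity in the distribution of both validation and derivation random samples".

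The last paragraph of Model Development sets a standard: "We expect the validation study to span across different domains (eg, inpatient vs outpatient, site, age group, and gender", on the ground that such a span is the best evidence that a prediction rule carries over to new patients. The next sentence cites the similar case mix of the two samples, and their being representative of the target population, as the reason for the conclusion: "we believe that the results of our validation tests will serve as strong evidence of generalizability".

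The article describes no held-out site, no held-out period and no external sample.

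**The concern.** The argument takes the similarity of the two samples as its evidence. A test of whether a model transports needs a difference between the data used for fitting and the data used for testing. Site, age group and gender are three of the four domains named in Model Development, and the split balances them across the samples and does not separate them. Agreement between the samples is then expected if the model is not overfitted, and pooled results say little about settings that did not contribute to the fit.

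The intended use makes this matter:

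- **Time and coding.** The Discussion plans deployment within the VHA record system. Variables Selection and Definition notes that ICD-10-CM came into VHA use only after the study period and is not used, while many structured predictors in Table 1 are ICD-9-CM codes.
- **Text format.** Scientific Rationale says that semistructured text has no standard layout, and Step 2b relies on rules built on that layout. If layouts differ by site or change over time, the extracted predictors may behave differently.

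A reader of the final report could take good hold-out results as proof that the model will hold in these changed conditions, which the design does not test.

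**Working it through.** **1. The stated split.** Input: N = 12,344 (Sample and Sampling—Complete).

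- 0.70 × 12,344 = 8640.8; stated 8641.
- 0.30 × 12,344 = 3703.2; stated 3703.
- 8641 + 3703 = 12,344. The figures reproduce.

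**2. Are the sites shared by both samples?** The Introduction gives 24 regional SCI centers. Actual site sizes are not given. The average is 12,344 / 24 ≈ 514. Even without stratification, the chance that a site of size m has no one in the 30% sample is about 0.7^m: 0.0008 for m = 20, and effectively zero for m = 514. Stratifying by site makes the overlap deliberate.

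**3. Are the periods shared?** The text does not say so directly. It follows because veterans of one FY 2009 cohort are assigned at random and calendar period is not a split factor.

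**4. What can pooled validation results show?** This is an illustrative simulation with 24 sites, N = 12,344, one predictor (intercept −0.6, mean slope 1) and 150 replicates. A site-stratified 70/30 split was compared with holding out 7 whole sites. All between-site SDs are assumptions. The table gives the SD across replicates of calibration-in-the-large (CITL, log-odds scale) and of the calibration slope.

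| Assumed SD, intercept / slope | CITL, planned split | CITL, sites held out | Slope, planned split | Slope, sites held out |
|---|---|---|---|---|
| 0 / 0 | 0.046 | 0.050 | 0.053 | 0.051 |
| 0.3 / 0.2 | 0.049 | 0.137 | 0.053 | 0.099 |
| 0.5 / 0.3 | 0.047 | 0.233 | 0.056 | 0.150 |
| 0.8 / 0.4 | 0.045 | 0.331 | 0.058 | 0.231 |

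Under the planned split, pooled calibration stays at its sampling noise whatever the site differences. With sites held out, the CITL spread grows to 0.331 / 0.045 ≈ 7.4 times the planned-split value in the last row. Mean AUC is nearly equal under both designs (0.71 to 0.74), so AUC would not reveal the difference. The simulated baseline risk, 1 / (1 + e^0.6) ≈ 0.35, is closer to the five-year incidence than to a one-year risk, so the table shows direction and not an expected size for this study.

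**5. What site variation could mean on the risk scale (hypothetical).** The article gives 4689 / 12,344 = 37.99% over the study period and no one-year figure. Assuming a constant hazard over five years, one-year risk = 1 − (1 − 0.3799)^(1/5) ≈ 0.0911. With an assumed between-site SD of the baseline log-odds, the central 95% of site risks is logit(0.0911) ± 1.96 × SD, back-transformed:

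- SD 0.2: 6.3% to 12.9%
- SD 0.3: 5.3% to 15.3%
- SD 0.5: 3.6% to 21.1%

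**The case against.** The strongest reply is that the claim concerns new patients in the population of interest, which is veterans with SCI in VHA care. The abstract states that "all VHA SCI centers were included in the analysis", and deployment is planned inside the VHA. For new veterans at those sites a patient-level random split is a fair test, and it can detect overfitting. This stands. It leaves later years and changed record-keeping as the larger gap, with unseen sites second.

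Four stronger readings are tempting, and the documents do not support them.

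- A reader might infer that poor calibration at particular centers must be averaged away. The sentence on domains can be read as planning results by domain within the validation sample, and stratifying by site would help that. The statement in the working therefore holds for pooled results only. Results by site from the planned split could show miscalibration, although those sites would still have helped to fit the model.
- A reader might infer that all the named domains are matched. Inpatient versus outpatient status is not a stratification factor.
- A reader might infer that the site ranges above are estimates. Both the 9.1% and the SDs are assumptions.
- A reader might infer that the validation is invalid. It is a legitimate internal validation, and the fault lies in the conclusion drawn from it.

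**Conclusion.** The point holds as an overclaim. A random split made alike by site, age group and gender supports a conclusion about reproducibility in veterans from the same sites and the same FY 2009-2013 window. It does not support generalizability to sites outside the fit, to later years, or to changed coding and templates. This follows from the design as the article states it and does not depend on the simulation.

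Its numerical size cannot be fixed from the documents, since they report neither between-site variation nor one-year incidence. The comparisons under Hypotheses 1 to 3 are unaffected as comparisons within this population.

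**What to change.** **Minimum (wording only).** Call the 70/30 split internal validation, and limit the conclusion to veterans from the same sites and period. Remove the inference from similar case mix to generalizability.

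**Recommended.** Add internal-external cross-validation on the extracted data. Leave out one site at a time, refit the model, and report AUC, calibration intercept and calibration slope per site, with a random-effects summary and a prediction interval. Use whatever site unit the split uses: the article does not define it, and the Introduction describes both 24 centers and 135 local care teams. Small units will give imprecise estimates per site. State that this does not retest the text-extraction rules, which are developed once on pooled documents (Steps 1 and 2).

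**Optional.** A temporal check. It is not part of the same loop: with one FY 2009 cohort, a later-year test reuses members who survived and remained at risk, and the analysis must account for that. Without such a check, make no claim about later periods.

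**Cost.** The wording change costs nothing. The site loop is modest extra analysis with existing data, and its results may look less favourable. The temporal check is additional work.
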